## Methods/design

In the following description of the design of the Mental Vitality @ Work study we follow the CONSORT statement, which aims to improve the quality of reporting randomized controlled trials (RCT) [21,22].

### Study design

A cluster randomized controlled trial with three parallel arms will be performed in order to evaluate the effectiveness of two strategies for a WHS mental module for nurses and allied health professionals: the OP-care strategy and the E-mental health strategy. The study combines two separately funded substudies. Substudy 1 will compare the control arm with the OP-care arm - a screening on mental health complaints and impaired work functioning followed by a consultation with an OP and appropriate interventions if necessary. Substudy 1 will test the effect on help-seeking behavior, work functioning and mental health of employees with problems in mental health and/or work functioning.

Substudy 2 will compare the E-mental health arm - a screening on mental health complaints and impaired work functioning followed by a tailored choice of self-help e-mental health interventions - with the control arm and with the OP-care arm. Additionally, a subgroup analysis of the healthy participants comparing the E-mental health arm with the OP-care arm will be conducted. Substudy 2 will test the effect of the interventions on work functioning and mental health.

Participants will be followed for six months. Two follow-up measures will be conducted, one at three months and one at six months. The Medical Ethics Committee of the Academic Medical Center in Amsterdam (AMC) gave approval for the study. Figure 1 presents an overview of the study design. Below, differences between Substudy 1 and Substudy 2 are described. Otherwise, the information is equal for both parts.

**Figure 1 F1:**
[figure not shown]
**Study design**.

### Setting

The study will be performed in one Dutch academic medical center, a hospital with 7000 employees and 1102 beds. The organization has its own in-company occupational health service. Each of the different divisions in the medical center has one OP assigned for its occupational health care. In the Dutch occupational health care system, OPs fulfill preventive tasks, have the duty of detecting occupational diseases and provide (return-to-work) counseling for sick-listed employees. In the Netherlands, if they are reported sick, workers are required to visit their OP for independent judgment of sick leave and for return-to-work guidance. Furthermore, all workers can make use of the free accessible consulting hour for employees with questions about work and health [23]. According to the in-company occupational health service, usage of the free accessible consultations by employees is limited.

### Study population

The research population includes all nurses, including surgical nurses and anesthetic nurses, and allied health professionals working at one Dutch academic medical center. In total, 1731 nurses and allied health professionals work in the medical center in 86 different wards, including outpatient wards. Employees who are sick-listed at the start of the study and expected to be on sick leave for more than two weeks are excluded from the study, as they will in any case consult an OP.

### Recruitment of participants

For a successful intervention study in a work setting, all layers of the organization must fully support the study. As we received endorsement from the board of directors, the nurse directors and the workers' counsel to perform the study, the likelihood for the departments to accept participation is high and all departments are expected to participate. During the enrollment period, information will be given on the hospital intranet, posters will be put up in the hospital building and flyers will be given out to promote the study.

Prior to the recruitment of individual employees, all wards will be informed about the Mental Vitality @ Work study by personal letters to the nurse directors and head nurses and the managers of allied health professionals. Subsequently, the individual workers will be informed by a letter to their home address with detailed information about the study procedure and about the safety and privacy of the individuals. Ten days later, an e-mail will be sent to the employees' work-email account, encompassing study information, a link to the online questionnaire and a personal log-in name and password. Agreeing with the informed consent, which is shown online prior to the questionnaire, is a prerequisite for starting the questionnaire. It will be possible for participants to log in on the website at any time and from any computer. It is also possible to log out at any point during the survey and to continue after logging in again. In the four weeks after the invitation for the study, three reminders will be sent to employees who have not yet started or completed the questionnaire.

### Interventions

#### OP-care

The first WHS mental module strategy encompasses an online screening for mental health complaints and work functioning problems plus an optional consultation with an OP for employees with mental health problems and/or work functioning problems. Directly after filling out the screening questionnaire, participants will automatically receive digital feedback on the screening results. Participants who score above a cut-off point for either the mental health complaints, work functioning impairments or both will receive an invitation from the in-company occupational health service for a face-to-face consultation with their OP scheduled within two weeks after filling out the screening questionnaire at baseline. The consultation is voluntary and supervisors of employees will not be informed about the invitation or the content of the consultation with the OP.

In order to structure the consultation of the OP, a seven-step protocol will be applied. The seven steps are: 1) discussing expectations; 2) discussing screening results and characteristics of mental health/work functioning complaints; 3) discussing possible causes in the private, work and medical situation and consequences for performing the work; 4) giving a diagnosis and offering a rationale; 5) giving advice for reduction of health complaints and for the improvement of work functioning and the prevention of incidents at work and discussing communication with the supervisor; 6) discussing a possible follow-up trajectory or referral to other care givers; and 7) summarizing the consultation.

This protocol closely follows the care as usual of the OPs. It was developed by means of interviews with the five participating OPs and based on the evidence-based guideline for OP's treatment of workers with mental health problems, which was developed by the Dutch Society of Occupational Medicine [11,24]. The main difference with the care as usual is the focus on identifying impairments in work functioning and giving advice on the improvement of work functioning and the prevention of consequences of impaired work functioning. All participating OPs were trained in using the protocol for the consultations.

#### Control group

In the control arm, participants will fill out the baseline questionnaire; however, results of the screening-questionnaires will not be reported back to participants, and no further interventions will be advised at baseline. As compensation, participants in the control arm will receive their personal screening results together with a tailored choice for a self-help e-mental health intervention six months after baseline, which is identical to the intervention in the E-mental health arm at baseline.

For ethical reasons, a suicide-risk protocol is implemented in all study arms. Participants identified as being at high risk of suicide will receive immediate feedback on their self-reported suicide risk. They will be advised to seek help instantly, and they are asked to choose between either contacting their general practitioner or receiving an invitation for an urgent consultation with their OP.

### Co-interventions

To our knowledge, no co-interventions on the organization or ward level aimed at mental health or work functioning improvement will be taking place in the medical center at the time of this study.

### Measures

#### Screening instruments used at baseline

##### Impaired work functioning

Impaired work functioning will be measured using the job-specific Nurses Work Functioning Questionnaire (NWFQ) ([name], [name], [name], [name], unpublished). The NWFQ aims to measure impaired work functioning due to CMDs in nurses and allied health professionals. This 50-item self-report questionnaire consists of seven subscales: 1) *cognitive aspects of task execution and general incidents*; 2) *impaired decision making*; 3) *causing incidents at work *(not applicable for allied health professionals); 4) *avoidance behavior*; 5) *conflicts and annoyances with colleagues*; 6) *impaired contact with patients and their family*; and 7) *lack of energy and motivation*. Cronbach's alphas vary between 0.70 and 0.94. Response formats vary between 5-category and 7-category scales; however, the number of categories is the same for all items of one subscale. The content of the response scales varies between Likert-type scales (0 = *totally disagree *to 6 = *totally agree*; 0 *= disagree *to 4 = *agree*; 0 = *no difficulty *to 6 = *great difficulty*), relative frequency categories (0 = *almost never *to 6 = *almost always*; *0 = almost never *to 4 = *almost always*), and absolute frequency categories (0 = *not once *to 6 = *in general more than once a day*). Sum scores of the subscales range from 0-100. As yet, no validated cut-off scores exist for this fairly new questionnaire. Based on prior data of the study population ([name], [name], [name], [name], unpublished), cut-off values were calculated according to the following principle. Sumscores on the different subscales can lead to three categories: green, orange, and red. Therefore, two cut-off values are set, at the 67th percentile and at the 75th percentile of participants with mental health complaints. In two of the 7 subscales (subscale 2 and 4) the cut-off values for orange and red were identical due to little variation; in this case, cut-off values were set at the 75th and 85th percentiles of participants with mental health complaints. For the total NWFQ, a red score on one subscale or three or more orange scores will lead to case identification of impaired work functioning. In the prior dataset, this resulted in 31% of the total sample.

##### Distress

Distress will be measured with the distress subscale of the Four-Dimensional Symptoms Questionnaire (4DSQ) [42,43]. The 16-item questionnaire uses a 5-point response scale (0 = *no*, 4 = *very often*) and has a Cronbach's alpha of 0.90 [43]. For case identification, a cut-off point of ≥11 will be applied [44].

##### Need for recovery

Early symptoms of work-related fatigue will be measured using the Need for recovery subscale of the Dutch Experience and Evaluation of Work (Dutch: VBBA) questionnaire [45]. The 11-item questionnaire with dichotomous response categories (*yes, no*) has a Cronbach's alpha of 0.86 [46-48]. A cut-off point of ≥6 will applied. This gives a sensitivity of 0.72 and a specificity of 0.79 [49].

##### Alcohol use

To measure risky drinking behavior, the 3-item AUDIT-C will be used. The three items ask for frequency of specific drinking behavior, varying in formulations for the items [50]. Two items have a 5-point response scale, and 1 item has a 6-point response scale. The cut-off score is ≥5 for men with a sensitivity of 90.9 and specificity of 68.4 and ≥4 for women with a sensitivity of 92.4 and specificity of 74.3 [51].

##### Depression and Anxiety

Depression and anxiety will both be measured with the corresponding subscales of the Brief Symptom Inventory (BSI) [52]. Each subscale has six items with a 5-point response scale (0 = *not at all*, 4 = *extremely*). Cronbach's alphas are 0.87 for both scales [52]. For both subscales, mean scores of ≥0.42 are used for case identification, with a sensitivity of 0.86 and a specificity of 0.66 for depression and a sensitivity of 0.83 and a specificity of 0.62 for anxiety [53].

##### Suicide risk

One item of the BSI depression subscale asks for suicidal thoughts. An answer on this item in one of the upper two response categories (*rather a lot *or *extremely*) will identify a person as being at high risk for suicide.

##### Panic disorder

The panic module of the Patient Health Questionnaire (PHQ-15) will be used for the assessment of panic disorders; however, it will only be used in participants identified as having anxiety complaints [54]. The 15 items have dichotomous answering categories (*yes, no*) and a Cronbach's alpha of 0.80 [55]. For case identification, we use the following procedure: two answers affirmative on the first four items plus four symptoms affirmative on the following 11 items. This identification procedure has a sensitivity of 0.91 and a specificity of 0.88 [56].

##### Post traumatic stress disorder

Post traumatic stress disorder is measured by the Schok Verwerkings Lijst (SVL) [57], a Dutch translation of the Impact of Event Scale [58]. The 15 items can be answered on a 4-point response scale (0 = *not at all*, 3 = *often*). Van der Ploeg et al. [59] found a Cronbach's alpha of 0.94 in a work-related sample. A cut-off point of ≥26 is applied [60].

##### Work relatedness of mental health complaints

Work relatedness of mental health complaints is measured by one item: "Do you think that your work has negative consequences for your mental health?" This self-formulated item has a dichotomous response scale (*yes, no*).

At T2, the same screeners will be used in the control arm.

#### Primary outcomes measured at baseline, three month follow-up and six month follow-up

##### Substudy 1

The primary study parameter of the comparison between the OP-care arm and the control arm is help-seeking behavior. It regards formal help sources that the subject has used during the past three months. In the operationalization of formal help sources, 11 help sources are presented (i.e., psychologist, psychiatrist, general practitioner, OP, physiotherapist, supervisor, coach, in-company social worker, social worker, religious counselor, alternative therapeutic treatments). The list of help sources is developed in analogy with earlier studies on help-seeking behavior [61-64].

The outcome measure help-seeking behavior is dichotomized into 'did seek formal help' for participants who had made use of any of the 11 caregivers and 'did not seek formal help' if none of the 11 caregivers were visited.

##### Substudy 2

The primary outcome measure of the comparison of the E-mental health arm with the OP-care and the control arm is work functioning, operationalized as job-specific impairments in work functioning. It will be measured using a total score of the Nurses Work Functioning Questionnaire (NWFQ).

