##### Absenteeism

Three items from the Productivity and Disease Questionnaire (PRODISQ) Module C are used to measure absenteeism from work. Absenteeism is operationalized as number of days on sick leave during the last three months and number of periods of sick leave during the last three months [65].

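### The help-seeking outcome's unanchored three-month look-back equals the follow-up interval, so a late three-month reply can leave the early occupational-physician consultation uncounted

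*Protocol article*

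**What the plan says.** All references are to the protocol article.

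- **Outcome (primary outcomes, Substudy 1).** "It regards formal help sources that the subject has used during the past three months". The score is dichotomous, positive "for participants who had made use of any of the 11 caregivers". The OP is one of the 11. The same outcome is measured at baseline, three months (T1) and six months (T2).
- **Follow-up times (Study design).** "Two follow-up measures will be conducted, one at three months and one at six months".
- **Intervention contact (OP-care).** Participants who screen positive are invited to a consultation "scheduled within two weeks after filling out the screening questionnaire at baseline". "The consultation is voluntary", and its sixth step is "discussing a possible follow-up trajectory or referral to other care givers".
- **Analysis (Effect evaluation).** Proportions are compared between arms by Chi-square test at each measurement time, with GEE models for change at T1 and T2.
- **Reply times.** Only the recruitment section touches on these, and there for the baseline form alone: "In the four weeks after the invitation for the study, three reminders will be sent to employees who have not yet started or completed the" (the sentence ends by naming that form). Nothing comparable is given for T1 or T2, and the article does not say whether they are timed from each participant's own baseline date.

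**The concern.** The look-back and the interval between questionnaires have the same length. Unless T1 is answered exactly three months after the participant's own baseline, the look-back does not start at baseline. Any shift moves its early edge, which is where the OP-care arm has its scheduled contact. Control participants receive no feedback or advice at baseline, so nothing in the design makes their contacts cluster there.

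The outcome is any-versus-none, so losing a single contact can change a participant's score. The Chi-square test is run separately at each time, so a loss at T1 enters the T1 comparison directly. T2 looks back only to about month three and cannot restore it. The recall period is part of the stated outcome definition, and no later analysis can recover contacts that the questionnaire did not ask about.

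**Working it through.** **1. The plan's own figure.** Inputs from the Sample Size section: 17% versus 34%, two-sided alpha 0.05, power 0.80. The uncorrected two-proportion formula gives 103 per arm; with continuity correction it gives 114, the stated number. Then 114/0.50 = 228 and 228/0.90 = 253.3, rounded up to 254. The sample size is reproduced and is not in error on this point.

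**2. Where the window starts.** Let *b* be the day of the baseline questionnaire and *a* the day T1 is answered, with three months taken as 91 days. A literal look-back starts *g* = *a* − *b* − 91 days after baseline.

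- *g* > 0: days 0 to *g* after baseline are outside T1. Example: *b* = 0, *a* = 98 gives *g* = 7, so a day-5 consultation is missed.
- *g* < 0: pre-baseline days are included. Example: T1 sent on a common date, *b* = 20, *a* = 100 gives *g* = −11, so 11 days before baseline are counted.

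**3. Share of consultations outside the window.** This is the probability that the consultation day is below *g*. The distribution of days is not given, so two assumptions are shown:

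| Delay *g* | Days uniform 0–14 | Days uniform 7–14 |
|---|---|---|
| 3 days | 3/14 = 21% | 0% |
| 7 days | 7/14 = 50% | 0% |
| 14 days or more | 100% | 100% |

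Contacts spread evenly over 91 days lose 7/91 = 8% at a 7-day delay, so the loss would differ between arms.

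**4. What this could do to the T1 comparison.** Let *s* be the share of the planned 17-point gain due to people whose only counted contact is the consultation, and *m* the share of consultations missed. The observed OP-care rate is *p*₂ = 0.34 − 0.17·*s*·*m*, with the control rate *p*₁ held at 0.17. With *n* = 114, *p̄* the mean of the two rates and *d* = *p*₂ − *p*₁, continuity-corrected power is

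Φ{[(*d* − 1/*n*)√*n* − 1.96√(2*p̄*(1−*p̄*))] / √(*p*₁(1−*p*₁) + *p*₂(1−*p*₂))}.

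At *m* = 0 this gives 0.80, as planned. With days uniform over 0–14, the same delay for everyone and day-exact recall:

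| Delay | *s* = 1 | *s* = 0.5 | *s* = 0.25 |
|---|---|---|---|
| 3 days | 30.4%, power 0.60 | 32.2%, 0.71 | 33.1%, 0.76 |
| 7 days | 25.5%, power 0.29 | 29.8%, 0.56 | 31.9%, 0.69 |
| 14 days or more | 17.0%, no difference | 25.5%, 0.29 | 29.8%, 0.56 |

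With days 7–14, the first two rows return to 34% and 0.80. The tables show sensitivity; neither is an estimate.

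**The case against.** The other side has a good deal of weight.

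- **Item wording is not shown.** The article gives a one-sentence summary. That the look-back runs from the day of answering is the natural reading, but it is not stated. This stands as a limit on certainty.
- **Late T1 replies are not documented.** A reader might carry the four-week reminder period over to T1: with delays uniform over 0–28 days and consultations uniform over 0–14, 1 − 7/28 = 75% would be missed. The document does not support this. The reminders concern recruitment of all invited staff and say nothing about reply times at follow-up.
- **Not every delay miscounts.** A miscount requires a delay longer than the consultation day, no other contact with any of the 11 sources in the window, and recall accurate to the day. A follow-up visit or referral keeps the score positive, and few respondents would exclude an early consultation by calendar arithmetic. This reduces the size considerably.
- **The error need not go one way.** If T1 goes out on a common date, late baseline completers may report pre-baseline use. This is correct, and it has the same cause and the same remedy.
- **Consultations are recorded elsewhere.** The process evaluation collects objective uptake of the invitation and an OP checklist. These allow under-reporting to be checked, but they cover the OP-care arm only and cannot replace an outcome that must be measured alike in both arms.
- **Anchoring breaks the match with the baseline item.** This also stands, as a modest cost of the remedy.

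**Conclusion.** The point holds as a weakness in the stated outcome definition, of undetermined size. The look-back equals the follow-up interval, no anchor is given, and the scheduled consultation lies at the window's early edge in one arm only. Read literally, a T1 reply delayed by more days than the consultation came after baseline drops that consultation for good. For participants with no other counted contact this biases the T1 comparison mostly towards no difference.

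T1 reply delay, consultation uptake and the share of help-seekers whose only contact is the consultation are not given. The illustrated loss at a 7-day delay runs from 0% to 50% depending only on the assumed consultation days, and loose recall and later contacts would lower it further. A reader might infer that the trial is bound to lose most of its power, or that every late reply is miscounted. The document supports neither. The case for acting is that the risk falls on a primary outcome and is cheap to remove.

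**What to change.** - Keep the three-month look-back at baseline, where there is no earlier questionnaire to refer to.
- Time T1 and T2 from each participant's own baseline date.
- Word the help-seeking item at T1 as *since you completed the first questionnaire on [date]*, and at T2 as *since your previous questionnaire on [date]*. The online system already uses personal log-ins and could display the date.
- Report window length by arm and use it in a sensitivity analysis only. It is measured after randomisation and has no place in the planned Chi-square test, so it should not be a covariate in the primary comparison.
- The absenteeism item, which asks for the "number of days on sick leave during the last three months", comes from a standard questionnaire and need not be reworded for this purpose.

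The cost is a wording change and date display in two online questionnaires. Follow-up windows will vary with reply delay and will no longer match the baseline item exactly. The planned rates and the 114 per arm are unaffected.

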#### Secondary outcomes measured at baseline, three month follow-up and six month follow-up

Secondary outcomes of both Substudy 1 and Substudy 2 are mental health complaints and absenteeism. The secondary outcomes that are only measured for Substudy 1 are work functioning and additional help-seeking information (intention to seek help, work as content of the consultation, frequency of visits, and informal help-seeking behavior). The secondary outcomes that are only measured for Substudy 2 are work ability, turnover intention, wellbeing, and work productivity.

